## Enrollment

Excluded (n= …)

- Not meeting inclusion criteria (n=…)
- Declined to participate (n=…)

**Assessment of eligibility (n=…)**

## Permuted block randomized allocation (n=90)

## (T0)

## Baseline measurement

**Arm** **C** (n=30)

- Received polyethylene cover (Left eye) & artificial teardrops (Right eye)

**Arm** **A** (n=30)

- Received artificial teardrops (Left eye) & normal saline (Right eye).

**Arm** **B** (n=30)

- Received polyethylene cover (Left eye) & normal saline (Right eye)

Analyzed (n=30)

Analyzed (n=30)

## Analysis

## (T1)

## 5 days following T0

Patients completed interventions C **(n=…)**

- Leaving follow-up (= 25%)

Patients completed interventions A **(n=…)**

- Leaving follow-up (= 25%)

**Analyzed (n ≥ 25 patients)**

- Left eyes (n ≥ 25)
- Right eyes (n ≥ 25)

**Analyzed (n ≥ 25 patients)**

- Left eyes (n ≥ 25)
- Right eyes (n ≥ 25)

Patients completed interventions B **(n=…)**

- Leaving to follow-up (= 25%)

## Analysis

**Analyzed (n ≥ 25 patients)**

- Left eyes (n ≥25)
- Right eyes (n ≥ 25)

**Figure 1 CONSORT flow diagram**

- 1. ***Sample size calculation***

The sample size is calculating according to the formula below.

$$n=\left[ \frac{\left( Z_{1-\alpha/2}\sqrt{p_{1}\left( 1-p_{1} \right)} \right)+\left( Z_{1-\beta}\sqrt{p_{2}\left( 1-p_{2} \right)} \right)}{d} \right]^{2}$$

With an 80% power and a 2-sided significance level of α = .05, and the probability of incidence of OSD of a study in which 3.6% (= p_1_) of patients had a positive fluorescein test in the simple eye ointment group and 20.2% (= p_2_) of patients had a positive fluorescein test in the eyelid taping group [5], the number of people needed in each group is 25. Anticipating a total attrition rate of 20%, a total of 90 patients will be included in the study, 30 patients for each arm.

- 1. ***Participants and recruitment***

Patients in the three ICUs in university-affiliated hospitals located in Malayer, Iran, will be recruited:

*2.4.1. Inclusion criteria*

- Newly being admitted to the ICUs;
- Having 18 years of age or older;
- Being comatose (with a Glasgow Coma Scale (GCS) less than or equal to 8 of 15);
- Undergoing mechanical ventilated;
- No trauma in the areas of the face and eyes;
- No history of chronic disease, electrolyte imbalance, cataract surgery or glaucoma;
- Absence of blinking (less than five times per minute); and
- Having a healthy cornea.

*2.4.2. Exclusion criteria*

- Presence of consciousness or natural blinking reflexes;
- Requiring cardiopulmonary resuscitation during the trial;
- Getting discharged from ICUs to the other centers or death.
  1. ***Implementation of the Interventions***

All patients will be received routine eye care. Routine eye care is consisted of eye irrigation with sterile normal saline when necessary (PRN) in all our ICUs. In addition to this usual care, prior to applying the planned interventions, the participants’ eyelids and surrounding skin will be gently irrigated by sterile normal saline and sterile gauze in the same way. The interventions are as below:

- For the intervention with artificial teardrops, while pulling down the lower lid of the patient’s eye to form a V pocket, two Tearlose (Miscellaneous) drops will be applied every six hours.
- For the intervention with normal saline, two drops of saline 0.9% will be applied in the same manner and dose.
- For the intervention with a polyethylene eye cover, 2.5-inch square pieces of thin plastic film will be put from the above of the eyebrow to the cheekbone and fixed by hypoallergenic paper tape.
  1. ***Outcome***

Assessments will be conducted using the statistical software SPSS version 16.0 for windows (SPSS Inc., Chicago, IL), setting the p-values at < 0.05. The measures used and measurements in the study are described in Table 1.

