The Ocular Surface Disease (OSD) is a common complication in patients who are admitted to Intensive Care Units (ICUs) but to receive minimal clinical consideration to prevent it [1, 2]. OSD is associated with different risk factors, as the impaired secretion and distribution of tear film over the ocular surface, tear components concentration due to lack of blinking, incomplete lid closure (lagophthalmos), and lid or conjunctival edema occurring with the use of a ventilator [3-8]. For these patients, there is a range of eye complications from mild conjunctival infections to serious everlasting ocular damage. Keratopathy (3.6% to 60%), chemosis (9% to 80%), and microbial keratitis are the most prevalent ocular disorders in ICU patients [9]. Insufficient eye care of ICU patients can increase the risk of serious eye problems such as corneal abrasions and ulceration, infectious keratitis, and even corneal perforation and loss of vision [10, 11].

- 1. ***Evidence-based Practice in Eye Care***

In recent decades, many pieces of evidence for eye care were developed; these practices include a wide range of interventions such as 1) washing the eyes with normal saline solution; 2) using lubricating ointments or teardrops; 3) moisturizing the chambers by applying a polyethylene eye cover (PEC), swimming goggles; 4) covering the eyes with eye shields, pads or patch; and 5) closing the eyelid with closure by transparent tape or tarsorrhaphy. There is no clear evidence as to which of these interventions represent the ideal eye care for ICU patients to prevent OSD [3, 4, 8, 10, 12-17]. There is confirmed that the healthcare professionals’ beliefs and traditions have played a major role in selecting eye care interventions in the ICU settings in different countries ICUs [4, 16]. Applying polyethylene eye covers has suggested as the most effective intervention [4] and the main components of the evidence-based protocol to prevent exposure keratopathy in the ICU settings [18]. But, in a very recent study of eye care for intensive care unit, the lubricants and taping of the lids are only advised for the conjunctival and corneal exposure [19]. The PEC was not considered as a part of the standard eye care for critically ill patients as well. So that, the standard care has been only comprised compromised a daily washing of eyelids with normal saline and sterile gauze and application of ocular lubricants at least twice per day in ICUs [20].

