- 1. ***Critical Appraisal for Context***

In Iran, washing out eye discharge with sterile normal saline is considered as part of routine eye care for ICU patients, but this intervention is not well supported empirically and is no longer recommended worldwide. Our research team collaborated with health professionals to select alternative eye care interventions to prevent OSD in ICU patients. The team members carefully reviewed empirical and clinical literature to determine the effectiveness or benefits and risks of alternative interventions, while also considering their feasibility in the local ICU contexts. The results of this critical appraisal indicated the following: 1) Irrigating eye with sterile normal saline could cause an increase in the incidence of OSD and cross-infection, and the cotton wool balls can cause corneal scratching [4]. 2) lubrication materials could be hard and time-consuming to apply on a regular or frequent time intervals by nurses [21]; further, the ointment containers can be infected if not used properly. 3) Using eyelid sutures makes regular eye checkups difficult; the sutures are also unpleasant in appearance and block the eye activities [21]. 4) Tarsorrhaphy is also invasive and almost impossible to apply to our lagophthalmos patients. 5) Moisture chamber goggles are only designed for adults and are inconvenient to use when patients are in a supine position [21]. Securing the moisture chamber goggles around the head also increases the risk of edematous eyes in ventilated patients. 6) Mechanical closure of the eyes is recommended in case of the lagophthalmos [22]. 7) Polyethylene covers may be pulled by infants, children or agitated patients [21]. Lastly, eye covering is claimed as the most effective intervention in preventing exposure keratopathy [4].

After examining the benefits and risks of each eye care interventions and its feasibility in our ICU settings, the research team decides to use polyethylene film and artificial teardrops versus normal saline. However, evidence to support their clinical efficacy in reducing the incidence and severity of OSD is limited.

1. **Materials and methods**
   1. ***Aim***

The aim of this is to compare the effects of the polyethylene film and artificial teardrops versus normal saline on the incidence and severity of OSD in comatose patients admitted to the ICU.

- 1. ***Study design***

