This is a prospective randomized triple-blinded three-armed clinical trial. We set up three arms ‘A’, ‘B’, and ‘C’ in which by tossing a coin, each eye of a patient will be allocated to one of three interventions: artificial teardrops, polyethylene covers, or normal saline eye drops. The groups will be as the following:

- Group “A”: patients received artificial teardrops for the left eyes and normal saline for the right eyes.
- Group “B”: patients received polyethylene cover for the left eyes and normal saline for the right eyes.
- Group “C”: patients received polyethylene cover to the left eyes and artificial teardrops to the right eyes.

Then, each eligible patient will be allocated to one of the three arms by permuted block randomization.

The study will be approved by the Research and Technology Vice-chancellor after confirming the proposal by the Research Ethics Committee at Hamadan University of Medical Sciences and registering in the Iranian Registry of Clinical Trials. We will conduct the study according to the ethical principles of the Helsinki Declaration of 2013 and follow the CONSORT 2010 statement (http://www.consort-statement.org). The study design is shown in Figure 1.

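### The 25 per group and 80% power rest on eye ointment versus eyelid taping, which the trial does not compare, and 80% is not reached even at those rates

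*Protocol*

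**What the plan says.** The aim is to "compare the effects of the polyethylene film and artificial teardrops versus normal saline on the incidence and severity of OSD in comatose patients". Under Study design, each patient receives one intervention per eye. Arm A sets teardrops against saline and arm B sets polyethylene film against saline. In arm C, "patients received polyethylene cover to the left eyes and artificial teardrops to the right eyes". Under Data Analysis, incidence is to be compared by McNemar's test.

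The sample size section opens "With an 80% power and a 2-sided significance level of α = .05". It then takes two rates from one cited study: 3.6% of "patients had a positive fluorescein test in the simple eye ointment group and 20.2" per cent of "patients had a positive fluorescein test in the eyelid taping group [5], the number of people needed in each group is 25". Allowing for 20% attrition, the plan enrols 90 patients, 30 per arm.

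The section does not say which intervention either rate stands for. The protocol gives no expected incidence for saline, film or teardrops. Its only background figures are general ones for ICU patients: "Keratopathy (3.6% to 60%), chemosis (9% to 80%), and microbial keratitis are the most prevalent ocular disorders in ICU patients".

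**The concern.** Power for a binary outcome depends on both event rates and, in a paired comparison, on how often the two eyes of a patient disagree. Here both rates come from treatments that are not given in the trial.

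The Introduction mentions lubricating ointments and teardrops together, so ointment could loosely stand in for teardrops, although the protocol does not say so. It lists lid closure by tape separately from saline washing and from polyethylene covers, so 20.2% has no obvious place in the trial. The tape that holds the film in place is a fixing and does not close the lid.

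Arm C is the hardest to defend. It compares two interventions that the Discussion groups together as evidence-based care, yet it is sized on the same 16.6-point gap as the saline comparisons.

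What is at stake is how the results are read. A reader who accepts 80% power for every arm may take a non-significant result as good evidence of no difference.

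**Working it through.** **Inputs from the sample size section.** p1 = 0.036, p2 = 0.202, two-sided α = 0.05 (z = 1.960), power 80% (z = 0.842), stated n = 25 per group. The symbol d is not defined; I assume d = p2 − p1 = 0.166.

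**Step 1: the plan's own figure.** The printed formula is n = [(1.960·√(p1q1) + 0.842·√(p2q2)) / d]², where q = 1 − p.
- √(0.036 × 0.964) = 0.1863 and √(0.202 × 0.798) = 0.4015.
- n = [(0.3651 + 0.3379) / 0.166]² = 17.9, so 18 and not 25.
- Swapping p1 and p2 gives 33. Using 90% power gives 29. Neither is 25.

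Each term carries the variance of one group only, which is a one-sample form. It is not the power calculation for a comparison of two groups.

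**Step 2: standard two-proportion calculation at the borrowed rates.** The mean rate is 0.119. √(2 × 0.119 × 0.881) = 0.4579 and √(p1q1 + p2q2) = 0.4426.
- Power at 25 per group = Φ[(0.166 × √25 − 1.960 × 0.4579) / 0.4426] = Φ(−0.15) = 44%.
- At 30 per group it is 51%.
- 80% power needs 59 per group.

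**Step 3: the planned test, McNemar, at the borrowed rates.** The within-patient correlation ρ is my assumption. The probability that both eyes are positive is p11 = p1p2 + ρ√(p1q1p2q2). The discordant cells are p1 − p11 and p2 − p11. Power is found by enumerating all outcomes.

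| ρ (assumed) | Discordant cells | Discordant proportion | Exact, 25 pairs | Asymptotic, 25 pairs | Exact, 30 pairs |
|---|---|---|---|---|---|
| 0 | 0.029, 0.195 | 0.22 | 22% | 44% | 33% |
| 0.2 | 0.014, 0.180 | 0.19 | 23% | 52% | 35% |
| 0.3 | 0.006, 0.172 | 0.18 | 23% | 57% | 37% |

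The exact figures are low because about 25 × 0.22 = 5.6 discordant pairs are expected. The exact test cannot reach p < 0.05 with fewer than six, even if all favour the same eye (2 × 0.5⁶ = 0.031, against 2 × 0.5⁵ = 0.063).

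**Step 4: the trial's own pairs.** No single figure can be given, because the protocol supplies no rates. The rates below are assumptions chosen only to show the range, at 25 per group or 25 pairs.

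| Saline v active (assumed) | Two-proportion power | n per group for 80% | Exact McNemar, ρ = 0 |
|---|---|---|---|
| 20% v 10% | 16% | 199 | 7% |
| 30% v 15% | 24% | 121 | 14% |
| 40% v 20% | 34% | 82 | 22% |
| 60% v 30% | 57% | 42 | 45% |
| 40% v 5% | 87% | 22 | 79% |

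Power runs from well under 20% to near or above 80%, depending on rates that the plan does not state.

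**The case against.** Borrowing rates from a neighbouring study is an ordinary planning choice. The cited study, by its title, concerned prevention of ocular surface disorders in ICU patients, and the protocol says its rates are fluorescein-test results, so setting and outcome are close. Ointment is a plausible stand-in for teardrops. Whether better rates for saline or film existed depends on sources not at hand. All this stands, and it limits the point to an unjustified and unlabelled proxy. It does not supply a counterpart for taping, a saline rate, or support for the gap in arm C. The protocol does describe eye covers as suggested to be the most effective intervention, which gives arm C a direction but no size.

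Four stronger readings are tempting and are not supported:

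- **That the saline rate must differ from 20.2%.** The protocol warns that "Irrigating eye with sterile normal saline could cause an increase in the incidence of OSD and cross-infection", but that concerns irrigation, whereas the saline intervention is two drops, and irrigation as needed goes to all patients. The 3.6% to 60% range is keratopathy in ICU patients generally, tied to no arm; enrolled patients must start with a healthy cornea and are assessed at five days. Neither fixes a saline rate.
- **That 80% is at least right for ointment versus taping.** Steps 1 to 3 show otherwise.
- **That film versus saline is the comparison to size on.** The aim gives film and teardrops equal standing.
- **That the sponsor plans to read a null result in arm C as equivalence.** The protocol does not say so; the risk lies in how a stated 80% would be used.

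**Conclusion.** The point holds. The rates behind 25 per group belong to interventions that the trial does not give, no rate is assumed for those that it does give, and the 80% is tied to none of the three within-patient comparisons. The figure also fails on its own inputs: about 44% by a standard two-proportion calculation at 25 per group, and with 25 pairs about 22-23% by exact McNemar or 44-57% by asymptotic McNemar. The McNemar figures assume a within-patient correlation of 0 to 0.3.

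A reader might infer that the trial is underpowered for its real comparisons. That is possible but not shown: with a large enough true effect, such as the assumed 40% v 5%, 25 pairs would come close to 80%. What is established is that the stated power is unsupported, and that arm C has the weakest basis.

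**What to change.** In the sample size section:

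1. Keep 30 per arm, and delete the claim that 25 per group gives 80% power. Do not relabel it as valid for ointment versus taping.
2. For each pair (teardrops v saline, film v saline, film v teardrops), state the expected rates, marked as assumptions, with a sensitivity range and an assumed discordant proportion. If ointment is meant as a proxy for teardrops, say so and justify it.
3. Tabulate McNemar power, or the detectable difference, at 25 to 30 pairs. State whether the exact or the asymptotic test is used, since the choice matters at this size.
4. State that the comparisons, arm C in particular, are not shown to have 80% power. Report each as a paired difference with a confidence interval, so that a non-significant result is not read as no difference.

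The cost is rewording and one small table, with no extra patients or procedures. The downside is a less favourable stated power.

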**Table 1. Study measures, source of measurement, and time of assessment.**

| **Construct** | **Questionnaire** | *Assessment times | | |
| --- | --- | --- | --- | --- |
|  |  | **S** | **T0** | **T1** |
| Demographic | Socio-demographic data | * | - | - |
| Clinical characteristics | Clinical history | * | - | - |
| Incidence of Ophthalmic Surface Diseases | The Corneal Fluorescein Staining Pattern | - | * | * |
| Severity of Ophthalmic Surface Diseases | The Corneal Fluorescein Staining Pattern | - | * | * |

*Assessment times: S= Screening, T0= baseline, T1= 5 days after the allocation.

*2.6.1 Primary outcome*

The incidence and severity of OSDs will be assessed with the Corneal Fluorescein Staining Pattern. The cornea will be examined at the slit lamp with a blue filter between four and eight minutes following fluorescein instillation. Punctate epithelial erosions (PEE) will be counted and scored from zero to six, the maximum possible score for each cornea. Grade 0 for no PEE, grade 1 for 1-5 PEE, grade 2 for 6-30 PEE, and grade 3 for more than 30 PEE. A score of severity will be added when the PEE is seen in the central 4mm diameter portion of the cornea, one or more filaments occurred anywhere on the cornea, or one or more patches of confluent staining, including linear stains, if found anywhere on the cornea.

- 1. ***Data Analysis***

In addition to descriptive statistics, the assumption of normality for numerical variables will be examined with the K-S test. Patients’ characteristics will be compared across the three treatment groups, using the Chi-Square test for categorical variables (sex, and type of injury) and one-way ANOVA for numerical variables (age). The incidence of OSD will be compared across the three treatment groups by McNemar’s test and the severity of the OSD by the Kruskal–Wallis test.

1. **Discussion**

This paper describes the evidence-based interventions added to the routine eye care for unconscious patients hospitalized in ICUs. It also presents the study protocol to compare the effectiveness of three methods of eye care, artificial teardrops, polyethylene covers, or normal saline eye drops using a prospective randomized triple-blinded three-armed clinical trial.

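### Section 2.3 feeds per-patient OSD rates into comparisons made between single eyes, with no conversion or justification, so the basis of the stated 80% power is unclear

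*Protocol*

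**What the plan says.** Protocol 2.3 (Sample size calculation) sets the error rates as "With an 80% power and a 2-sided significance level of α = .05". Its two inputs come from a cited study of other eye-care methods. The lower one, p1 = 3.6%, is the share of ointment patients who stained. The higher one is worded in the same way: "20.2% (= p_2_) of patients had a positive fluorescein test in the eyelid taping group". From these the section derives its size, stating that "the number of people needed in each group is 25", and it recruits 30 per arm to allow for attrition.

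The rest of the protocol works at the level of the eye:

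- **Treatment.** Under 2.2 (Study design), "each eye of a patient will be allocated to one of three interventions". In every arm the left and right eyes receive different interventions.
- **Randomisation.** Also under 2.2, "each eligible patient will be allocated to one of the three arms by permuted block randomization". The patient is block-randomised, and the arm fixes which eye gets which intervention.
- **Scoring.** In 2.6.1 (Primary outcome) the staining score has a ceiling described as "the maximum possible score for each cornea".
- **Counting and testing.** Figure 1 counts at least 25 left eyes and at least 25 right eyes per arm. The Data Analysis section tests incidence with McNemar's test, a paired method.

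**The concern.** In this design no intervention has a patient-level rate. A patient in arm A has one eye on teardrops and one on saline, so the incidence under either treatment is an eye rate. The inputs in 2.3 are worded as patient rates from separate groups of patients.

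The two coincide if the source counted one eye per patient, or if staining was always bilateral. They differ if a patient was called positive when either eye stained, because some of those patients had one clear eye. The eye rates would then be lower than 3.6% and 20.2%, and the difference to be detected would probably shrink with them. The protocol does not say which case applies, so a reader cannot tell whether the two inputs are the right quantities. At stake is how a null result is read: if the true power is well below 80%, no significant difference says little about whether the interventions differ.

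**Working it through.** **Inputs from 2.3.** Two-sided α = 0.05 (z = 1.96), power 80% (z = 0.8416), p1 = 0.036, p2 = 0.202, stated n = 25. The symbol d is not defined there; I take d = p2 − p1 = 0.166.

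**Assumption, not in the documents.** Source patients had both eyes under one method and were positive if either eye stained. The per-eye rate is then k times the patient rate, with k between 0.5 (never both eyes) and 1.0 (always both). Independent eyes give 1 − √(1 − 0.036) = 1.82% and 1 − √(1 − 0.202) = 10.67%.

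**Step 1: the plan's own figure.** The printed formula is n = [(1.96√(p1(1−p1)) + 0.8416√(p2(1−p2))) / d]².

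At the stated rates: [(1.96 × 0.1863 + 0.8416 × 0.4015) / 0.166]² = (0.7030 / 0.166)² = 17.9, so 18. The stated 25 is not reproduced. That is a separate matter; I use the printed formula here only to isolate the effect of the unit.

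**Step 2: the unit alone, with equal bilaterality in both source groups.** Inverting the same formula at n = 25 gives power = Φ[(5d − 1.96√(p1(1−p1))) / √(p2(1−p2))]. At the stated rates this is Φ[(0.830 − 0.3651) / 0.4015] = Φ(1.158) = 87.7%. At half the rates it is Φ[(0.415 − 0.2606) / 0.3013] = Φ(0.512) = 69.6%.

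| Per-eye rates | d | n, printed formula | Power at n = 25 |
|---|---|---|---|
| 3.6% vs 20.2% (k = 1) | 0.166 | 18 | 87.7% |
| 2.7% vs 15.15% (k = 0.75) | 0.1245 | 25 | 80.2% |
| 1.82% vs 10.67% (independent eyes) | 0.0885 | 35 | 72.1% |
| 1.8% vs 10.1% (k = 0.5) | 0.083 | 39 | 69.6% |

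The crossing point for 80% is therefore about k = 0.75.

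**Step 3: unequal bilaterality.** If k differs between the source groups, the extremes are:

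- 10.1% − 3.6% = 0.065, with printed-formula power 45% at n = 25;
- 20.2% − 1.8% = 0.184, with printed-formula power 95% at n = 25.

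The second difference is larger than the one assumed.

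**Step 4: the paired test the protocol names.** I apply McNemar's test to 25 left–right pairs within an arm. If the two eyes are uncorrelated at the stated rates, the discordant probabilities are 0.036 × 0.798 = 0.0287 and 0.202 × 0.964 = 0.1947. Expected discordant pairs are 25 × 0.2234 = 5.6. The exact two-sided test cannot reach 0.05 with fewer than six discordant pairs (2 × 0.5⁵ = 0.0625; 2 × 0.5⁶ = 0.031).

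Exact power is 22%, and it stays at 22% to 23% with a between-eye correlation of 0.2 or 0.35. With uncorrelated eyes it is 3% at 1.82% vs 10.67% and 2% at 1.8% vs 10.1%. The highest value anywhere in the range checked, including the favourable extreme of step 3, is about 31%.

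**The case against.** The strongest reply is that the unit effect depends on a source the protocol does not describe. If the cited study counted one eye per patient, or if staining was always bilateral, the conversion factor is 1 and nothing changes. Even under an either-eye definition, with equal bilaterality the printed formula keeps about 80% power at 25 down to a factor of about 0.75. All of this stands, and it rules out several stronger readings that a reader might infer:

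- **That the 80% is overstated because of the unit alone.** The documents do not establish this; it is conditional on how the source counted.
- **That the plan took the most favourable end, or that the difference is at most twice too large.** Under an either-eye definition, halving bounds each rate, but it does not bound the difference. The difference could be 0.184, above the assumed 0.166, or 0.065, which makes the assumed value about 2.6 times too large (0.166 / 0.065).
- **That single eyes are randomised.** Patients are block-randomised to arms. The stated 25 people matches 25 pairs per arm, so the count of units is not at fault; the rates attached to them are.
- **That the low McNemar power shows the unit problem.** The 22% arises at the rates as given, where the unit has no effect. It comes from the mismatch between the formula and the paired test.

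The reply does not supply the missing link. The inputs are worded per patient, the comparisons are per eye, and the protocol neither connects nor justifies them. New rates for the trial's own interventions would settle the matter only if they came with their unit stated.

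**Conclusion.** The point holds as an unjustified input to the primary sample size. Its effect on power is conditional. With an either-eye definition and equal bilaterality, the printed formula's requirement runs from 18 to 39 and its power at 25 from 88% to 70%. With unequal bilaterality the direction is not certain. With one eye per patient, or always bilateral disease, the effect is nil.

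What does not depend on the unit is that exact McNemar power with 25 pairs is about 22% at the stated rates. It does not approach 80% anywhere in the range examined. The paragraph should therefore be corrected whichever way the unit question is answered.

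**What to change.** In 2.3:

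1. State whether p1 and p2 are rates per eye or per patient in the cited study, and how a positive case was defined there.
2. If they are per patient, convert them to per-eye rates with a stated assumption on how often disease is bilateral. Show the range, allowing the assumption to differ between the two source groups.
3. Restate the power, or the per-eye difference detectable with 80% power, for the planned 25 evaluable pairs under McNemar's test, with a stated assumption on the correlation between a patient's two eyes.

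The cost is one recalculation, a rewritten paragraph and a less favourable stated power. No extra patients are needed, and neither the design nor the interventions change.

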**Effect of polyethylene film and artificial teardrops versus normal saline on the incidence of superficial ocular disorders in unconscious patients: a prospective randomized triple-blinded three-arm clinical trial**

**Background:** Polyethylene covers are claimed to be useful in preventing ocular surface diseases (OSD); however, evidence of their clinical efficacy is limited. This clinical trial aims to compare the effect of polyethylene film and artificial teardrops versus normal saline on the incidence of OSD in unconscious patients. This paper summarizes the study protocol.

**Method:** The design of the planned study is a multicenter randomized blinded three-arm clinical trial. Although we need 25 patients in each arm, anticipating a total attrition rate of 20%, a total of 90 patients will be selected and included in the study, 30 patients for each arm. We will set up three arms ‘A’, ‘B’, and ‘C’ in which each eye of a patient will be considered for one of three interventions: artificial teardrops, polyethylene covers, or normal saline eye drops by tossing a coin. Then, each eligible patient will be allocated to one of the three arms by permuted block randomization. All patients are unconscious so, their blinding does not apply. Both the eye observer and the analyzer will be unaware of the type of interventions. The patients’ eyes will be examined based on the Corneal Fluorescein Staining Pattern. The collected data will be analyzed by SPSS-16 software at a 95% confidential level.

**Discussion:** The results of this study will contribute to the developing pieces of evidence for a safe, effective, and accessible eye care intervention for preventing the incidence of OSD in comatose patients.

**Keywords**: Coma, Infectious Diseases, Eye, Intensive Care Units, Nursing Care, Patients.

1. **Introduction**

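### The stated 25 per group for 80% two-sided power does not follow from the protocol's own formula and inputs, and 25 pairs fall well short of 80% for the McNemar test it names

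*Protocol*

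**What the plan says.** All references are to the protocol.

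- **Sample size calculation.** It says that "The sample size is calculating according to the formula below" and prints n = [(Z(1−α/2)·√(p1(1−p1)) + Z(1−β)·√(p2(1−p2)))/d]². The symbol d is not defined.
- **Inputs.** "With an 80% power and a 2-sided significance level of α = .05"; "3.6% (= p_1_) of patients had a positive fluorescein test in the simple eye ointment group"; "20.2% (= p_2_) of patients had a positive fluorescein test in the eyelid taping group".
- **Result.** "the number of people needed in each group is 25". Then: "Anticipating a total attrition rate of 20%, a total of 90 patients will be included in the study, 30 patients for each arm".
- **Abstract.** It repeats the figure: "Although we need 25 patients in each arm, anticipating a total attrition rate of 20" per cent.
- **Flow diagram (Figure 1).** It expects at least 25 left and 25 right eyes analysed in each arm, and prints a 25% loss to follow-up.
- **Study design.** Each patient's two eyes receive different treatments, and each treatment is used in two of the three arms.
- **Data Analysis.** Incidence is to be compared across the three treatment groups by McNemar's test. No version (exact, continuity-corrected or uncorrected) is named.

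**The concern.** The formula, the inputs and the answer are all printed, so the calculation can be checked, and it does not close. The formula also has no variance term for a second group, although it is used to size groups that will be compared. Nor does it contain the quantity that drives the power of McNemar's test, the rate of discordant pairs.

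Incidence is part of the primary outcome. If the text stands, the trial will be reported as designed with 80% power. A non-significant result could then be taken as evidence that the treatments do not differ, when the named test had much less chance of detecting the planning difference.

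**Working it through.** **Inputs** (Sample size calculation): p1 = 0.036, p2 = 0.202, two-sided α = 0.05 (z = 1.960), power 80% (z = 0.8416). Assumption: d = p2 − p1 = 0.166, the natural reading of the undefined symbol.

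**1. The printed formula**

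√(0.036 × 0.964) = 0.1863; √(0.202 × 0.798) = 0.4015.

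- As printed: [(1.960 × 0.1863 + 0.8416 × 0.4015)/0.166]² = [(0.3651 + 0.3379)/0.166]² = 17.9, so **18**.
- Rates swapped: [(1.960 × 0.4015 + 0.8416 × 0.1863)/0.166]² = 32.3, so **33**.

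Neither is 25. Some departures from the text do come out near it:

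- one-sided 5%, 80% power, rates swapped: 24.2 (25);
- one-sided 5%, 90% power, rates as printed: 24.5 (25);
- the printed formula with an added continuity correction: 23.6 (24);
- the printed formula with d of about 0.141 instead of 0.166: 25.

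**2. A two-group formula with the same inputs**

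- Unpooled: (1.960 + 0.8416)² × (0.0347 + 0.1612)/0.166² = 55.8, so **56** per group.
- Pooled, mean rate 0.119: [(1.960 × √(2 × 0.119 × 0.881) + 0.8416 × √0.1959)/0.166]² = 58.5, so **59** per group.

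Power of 25 versus 25 (pooled): Φ[(0.166 × 5 − 1.960 × 0.4579)/0.4426] = Φ(−0.152) = **44%**. The trial has no such independent groups. This is only the benchmark for the protocol's own per-group framing.

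**3. The named test: McNemar on pairs within an arm**

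With between-eye correlation ρ, the probability that both eyes are positive is p11 = p1p2 + ρ√(p1(1−p1)p2(1−p2)). The discordant probabilities are p2 − p11 and p1 − p11. Since p11 cannot exceed 0.036, ρ cannot exceed about 0.38. At ρ = 0 the discordant probabilities are 0.1947 and 0.0287, so 25 × 0.2234 = 5.6 discordant pairs are expected. At the maximum ρ about 4.2 are expected. The exact two-sided test needs at least 6 discordant pairs to reach p < 0.05, since 2 × 0.5⁵ = 0.0625 and 2 × 0.5⁶ = 0.031.

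Power was found by summing binomial probabilities over the number of discordant pairs and their split, for ρ from 0 to 0.38:

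| Pairs per arm | Exact | Uncorrected |
|---|---|---|
| 25 (stated) | 22–23% | 44–61% |
| 30 (no loss) | 32–38% | 51–75% |
| 24 (30 × 0.80) | about 20% | 43–58% |
| 22 (30 × 0.75 = 22.5) | 15–16% | 39–51% |

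In the first two rows the continuity-corrected version gives the same power as the exact one. By normal approximation, 80% power needs about 62 pairs per arm at ρ = 0, falling to about 46 at the maximum ρ.

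**4. Using all three arms**

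With 25 completers per arm there are 50 eyes per treatment. Treated as independent, 50 versus 50 gives about 73% by the pooled formula, 78% by chi-square enumeration and 64% by Fisher's test. A simulation of a cluster-robust risk-difference model on all eyes used 2000 runs per setting, latent correlation 0, 0.5 or 0.7, and a teardrop rate of 3.6%, 10% or 20.2%. It gives about 77–88% for cover versus saline at 25 completers per arm, and about 71–83% at 22. These figures are for one contrast, without multiplicity adjustment.

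**The case against.** The strongest reply is that the patient numbers may be adequate even though the paragraph is wrong. Each treatment appears in two arms, so a per-group count of 25 understates the information, and a clustered analysis of all eyes comes near 80% for one contrast. This stands as a statement about 90 patients. It does not rescue the text, because neither the sample size section nor the Data Analysis section plans such an analysis.

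Three further objections limit what may be claimed:

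- **Version and pairing.** A reader might infer that the planned test has 22% power, full stop. The protocol names no McNemar version, and the uncorrected one gives 44–61%. Within-arm use is itself an inference: the text speaks of a comparison across groups, but differently treated pairs exist only within a patient.
- **Origin of 25.** A reader might infer that a one-sided test was used. More than one departure leads to 25, so the document does not settle where it came from. The mismatch also depends on reading d as p2 − p1.
- **Borrowed rates.** The 3.6% and 20.2% come from eye ointment and eyelid taping, neither of which is an arm here. The protocol says so openly, and planning from a related comparison is common. This is a remark about assumptions, not an arithmetic error.

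**Conclusion.** The statement that 25 per group gives 80% power at two-sided 5% is wrong as written. With d = 0.166 the printed one-sample formula gives 18 (33 with the rates swapped), and a two-group formula gives 56 to 59.

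For the named test at 25 pairs, power is about 22–23% (exact or continuity-corrected) or 44–61% (uncorrected). Even with no loss, 30 pairs reach at most about 75%, and only with the uncorrected test at the highest possible correlation. These figures rest on the protocol's two rates, on d being their difference, and on McNemar being applied within an arm.

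It would go too far to infer that the trial needs 56 to 59 patients per arm or that 90 patients cannot suffice. That benchmark belongs to an independent-groups design that this trial does not have. The defect is in the power justification and its link to the planned test. It should be corrected before results are reported, because incidence is a primary outcome.

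**What to change.** 1. Keep 90 patients.
2. Delete the one-sample formula and the statement that 25 per group gives 80% two-sided power, in the Sample size calculation section and in the abstract. Define d in whatever formula replaces it.
3. State which McNemar version will be used and on which pairs. Restate its power as a range over between-eye correlation, at the completers expected under the protocol's own attrition figures. Those figures need reconciling: 20% of 30 leaves 24, and 25% leaves 22.5, both below the 25 in the flow diagram.
4. Quote a power near 80% only if a clustered eye-level analysis over all three arms is adopted as primary. Give the contrast, the assumed correlation, the number of completers and the handling of multiplicity with it.
5. As a side remark, label 3.6% and 20.2% as assumptions taken from other interventions and show power over a range of rates.

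The cost is one rewritten paragraph, a short simulation and a stated power that is less favourable than the present one. No patients are added.
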